## Abstract

Background: Pressure injuries (PIs) represent a significant healthcare challenge in Singapore among the aging population. These injuries contribute to increased morbidity, mortality, and healthcare expenditure. Existing research predominantly explores single-component interventions in hospital environments, often yielding limited success. The INCA Trial aims to address this research gap by conducting a comprehensive, cluster randomized controlled trial that integrates education, individualized nutritional support, and community nursing care. This study is designed to evaluate clinical and cost-effectiveness outcomes, focusing on PI wound area reduction and incremental costs associated with the intervention. Methods: The INCA Trial employs a two-group, non-blinded, cluster randomized, and pragmatic clinical trial design, recruiting 380 adult individuals (age ≥ 21 years) living in the community with stage II, III, IV, and unstageable PI(s) who are receiving home nursing service in Singapore. Cluster randomization is stratified by postal codes to minimize treatment contamination. The intervention arm will receive an individualized nutrition and nursing care bundle (dietary education with nutritional supplementation), while the control arm will receive standard care. The 90-day intervention will be followed by outcome assessments extending over one year. Primary outcomes include changes in PI wound area and the proportion of participants achieving a ≥40% area reduction. Secondary outcomes include health-related quality of life (HRQOL), nutritional status, and hospitalization rates. Data analysis will be conducted on an intention-to-treat (ITT) basis, supplemented by interim analyses for efficacy and futility and pre-specified sensitivity and subgroup analyses. The primary outcome for the cost-effectiveness analysis will be based on the change to total costs compared to the change to health benefits, as measured by quality-adjusted life years (QALYs). Discussion: The INCA Trial serves as a pioneering effort in its approach to PI management in community settings. This study uniquely emphasizes both clinical and economic outcomes and melds education, intensive dietetic support, and community nursing care for a holistic approach to enhancing PI management.

## 1. Background

A pressure injury (PI) is defined as a “localized injury to the skin and/or underlying tissue usually over a bony prominence, as a result of pressure, or pressure in combination with shear” [1]. In Singapore, the majority of adults with stage III to IV PIs were community-acquired, [2] with a prevalence of 6% to 29% reported [3]. An incidence rate of 505 (95% CI: 493–517) per 100,000 persons has been reported, and it has been observed to increase with age, with the sharpest rise observed in individuals aged 80 years and above, at 3647 (95% CI: 3530–3766) per 100,000 persons [3,4].

PI(s) are associated with increased morbidity and mortality. Zhan and Miller [5] reported 3.98 days of extra hospitalization (*p* < 0.001) and 7.23% excess mortality (*p* < 0.001). Locally, one-fifth (20.0%) of patients had two or more PI-related readmissions for the index wound [6]. On subsequent follow-up one year later, the all-cause mortality rate was 14.3%, with 26.8% of patients institutionalized upon discharge from the tertiary hospital [6]. 

The most recent 2014 Cochrane review found no clear evidence that nutritional interventions reduce/heal PI(s) [7], but newer studies in recent years indicated potential benefits of using specialized nutritional feeds containing specific amino acids, such as arginine and leucine, as well as antioxidants, such as Vitamins C and E [8,9,10,11]. 

Integrated care is still in its development stages in Singapore and Asian countries, in comparison to the countries in North America and Europe [12]. Patients with PIs in Singapore are routinely reviewed by dietitians in acute care settings but rarely in the community upon discharge. This may be related to the failure to return for outpatient clinic reviews due to immobility and social reasons [13]. Furthermore, there is limited access to community dietitians and funding for dietetic review or nutritional support [14]. Most patients and their caregivers/family members also do not receive adequate nutritional education on PI treatment and prevention, as it is not a standard procedure in most healthcare settings. As a result, the majority of patients or caregivers do not have the necessary nutritional knowledge for PI management. 

Early nutritional studies on PI wound healing generally implement simple [15] single-component interventions using specialized medical nutritional supplements [16,17,18,19] or primarily concentrate on hospitalized patient populations, where the intervention period is inadequate to deliver a positive outcome [19,20]. Recently, a cluster randomized controlled trial (RCT) of 1600 hospitalized patients using a complex multi-component PI prevention intervention (posters/DVD and face-to-face education) showed a statistically non-significant reduced hazard ratio for new PI(s) developed [21,22]. However, one of the limitations of this study was the lack of individualized nutritional intervention with supervision.

To address this limitation and build on the body of work performed, we intend to conduct a cluster randomized controlled trial, implementing a multi-component PI care bundle intervention consisting of education, dietetic support with medical nutritional supplementation, and trained home care/community nurses in nutrition care, for patients in the community with existing PI(s) (stages II, III, IV, and unstageable). 

The objectives of this study are to evaluate the clinical and cost-effectiveness of the multi-component PI care bundle intervention on pressure injury-related outcomes. The primary outcomes for the cluster randomized controlled trial were the change in PI area from the baseline in the intervention and study period and the proportion of participants with a 40% or greater reduction in the wound area. The primary outcomes for the economic evaluation of the trial are the change to total costs to account for incremental costs of the trial intervention for the change to health benefits, measured by quality-adjusted life years (QALYs), and the primary endpoints of the clinical trial.

## 2. Methods/Design

Standard protocol items for reporting cluster RCT were followed using the Spirit statement [23] and the SPIRIT-OUTCOMES extension [24], with the Template for Intervention Description and Replication (TIDieR) [25] checklist used to guide the description of the study intervention. Refer to the Supplementary Material for the completed checklists.

### 2.1. Study Design

We intend to perform a two-group, non-blinded, cluster randomized, and pragmatic clinical trial with the recruitment of 380 subjects (190 per arm). The duration of the intervention will be 90 days, with data collection of outcomes performed over a one (1)-year period. 

### 2.2. Study Population and Setting

Adults (age ≥ 21 years of any gender) living in the community with stage II, III, IV, and unstageable PI(s) who are receiving home nursing services in Singapore (28 districts comprising 82 postal codes) were eligible. 

### 2.3. Inclusion and Exclusion Criteria 

Patients will be considered eligible if they are able to provide written informed consent (patient or legal guardian). The patients can be on oral and/or enteral nutritional support. The exclusion criteria for the trial are presented in Table 1.

### 2.4. Sample Size Estimation

The sample size calculation is based on the results reported by Cereda et al. [17], where an odds ratio (OR) of 2.0 for ≥ 40% improvement in wound area on patients receiving a specialized nutritional supplementation containing arginine is used. To have 80% power to detect this difference with a 2-tailed type I error of less than 5%, we require at least 144 subjects per arm. After assuming a 20% mortality and 10% withdrawal rate (based on a Cereda et al. [17] study of 16% mortality and 6% withdrawal and a Chaboyer et al. [22] study of 8% loss to follow-up), we plan to enroll a total of 380 subjects (190 per arm). As we will be undertaking an intention-to-treat (ITT) analysis, anticipated adherence will be one of the outcome measurements to determine if the intervention (education and supplementation) is acceptable to the participants (Supplementary Material Figure S1).

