### 2.5. Randomization

We will randomize patients into two groups using a cluster randomization method, where the patient population is stratified into two groups based on the locality (postal code) and a random 1:1 block allocation of postal codes (under the care of nursing teams) to either intervention or control group. The allocation of the groups will be concealed until participation is fully confirmed. 

The primary reason for cluster randomization is to limit treatment contamination between the intervention and control groups. As the nurses from home nursing services are allocated to the care of multiple patients within the same neighborhood (based on postal code), individual randomization may increase the risk of the control group learning about the nutritional intervention (type II error) from interactions with the assigned home care nurse.

We will engage a statistician who is not associated with recruitment to generate a random number list to determine the order in which the recruiting staff will visit the specified postal codes for participant recruitment. Postal codes with low residential density in Singapore (limited cluster size) may be excluded or combined with other postal codes if feasible. 

We aim to recruit 8 to 10 subjects per week and finish recruitment in 35 to 50 weeks. We determined this rate of recruitment as there are currently 500 to 600 individuals under home nursing care with known PI(s), with the expectation that 20% to 30% of individuals will not meet the selection criteria. For patients with multiple wounds, all the PI(s) in stages II and above will be included in the analysis.

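### Section 2.4 sizes a trial that randomises postal codes as if it randomised patients, so the stated 80% power carries no allowance for clustering

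*Protocol article*

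**What the plan says.** Section 2.5 makes the postal code the unit of randomisation: "a random 1:1 block allocation of postal codes (under the care of nursing teams) to either intervention or control group". The reason given is that home-care nurses look after several patients in one neighbourhood. Section 2.2 gives the only cluster count in the document, "28 districts comprising 82 postal codes", and section 2.5 allows sparsely populated codes to be left out or merged.

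Section 2.4 sets out the sample size as a complete chain. The effect is "an odds ratio (OR) of 2.0 for ≥ 40% improvement in wound area", the target is "To have 80% power to detect this difference", and the result is "with a 2-tailed type I error of less than 5%, we require at least 144 subjects per arm". The last step begins "After assuming a 20% mortality and 10% withdrawal rate" and ends at 190 per arm, 380 in total. No ICC, cluster size, cluster count or design effect appears.

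Elsewhere clustering is recognised. Section 5.1 plans patient-level and cluster-level analysis with a mixed-effects Cox model. Section 5.5 says the sample size might be reassessed at the interim looks, without mentioning clustering.

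**The concern.** Patients in one postal code share nurses. By section 2.7 the nurses who give the care also measure the wounds, unblinded, and attend one arm only. Both care and outcome measurement are therefore shared within clusters, and on the protocol's own account an ICC of zero is hard to defend. With a positive ICC, 144 patients per arm carry less information than 144 independently randomised patients.

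The 80% is the benchmark against which a null result would be read, and the starting point for any reassessment under section 5.5. If it leaves out clustering, a null result looks more informative than it is and the reassessment starts from the wrong figure.

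**Working it through.** **Inputs from the protocol.** Odds ratio 2.0, 80% power, two-sided 5%, 144 per arm, 20% mortality plus 10% withdrawal, 190 per arm (2.4); 82 postal codes (2.2).

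**Not given, so assumed.** Control-arm proportion (scanned); ICC 0.01 / 0.02 / 0.05 / 0.10; variation in cluster size; any cluster count below 82.

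**1. Reproducing 144.** With control proportion p0, the treated proportion p1 follows from the odds ratio of 2.0. The pooled two-proportion formula, with p̄ the mean of p0 and p1, is

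n = [1.960 √(2p̄(1−p̄)) + 0.842 √(p0(1−p0) + p1(1−p1))]² / (p1−p0)²

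- Uncorrected: the minimum over all p0 is about 132, near p0 = 0.41. It gives 144 at p0 of about 0.28 or 0.56.
- Continuity-corrected: the minimum is 144, at p0 of about 0.39 to 0.44.

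Both are individual-randomisation formulas, so 144 needs no design effect to explain it. A hidden one could be at most 144/132 = 1.09, and only at the most favourable unstated control proportion.

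**2. The step to 190.** 144 × 1.3 = 187, close to 190. Dividing instead gives 144/0.70 = 206, or 144/(0.8 × 0.9) = 200. Both exceed 190, so this step holds no reserve for clustering.

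**3. Power with clustering.** Take 144 independent patients per arm as giving exactly 80%, with n analysed per arm and k clusters in total:

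m = 2n/k; DE = 1 + [(1 + CV²)m − 1] × ICC; power = Φ[(1.960 + 0.842) √(n/(144 × DE)) − 1.960]

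For n = 144, k = 82 and equal sizes, m = 288/82 = 3.51. At ICC 0.05, DE = 1 + 2.51 × 0.05 = 1.126, and power = Φ(2.802/√1.126 − 1.960) = Φ(0.68) = 75%.

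| Analysed per arm, clusters | ICC 0.01 | 0.02 | 0.05 | 0.10 |
|---|---|---|---|---|
| 144, 82 equal clusters: DE | 1.03 | 1.05 | 1.13 | 1.25 |
| 144, 82 equal clusters: power | 79% | 78% | 75% | 71% |
| 144, 82 clusters, assumed CV 0.7: power | 78% | 77% | 72% | 65% |
| 144, assumed 40 equal clusters (m = 7.2): power | 78% | 75% | 69% | 60% |

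**4. Attrition, kept separate.** A 30% loss from 190 leaves 190 × 0.70 = 133 per arm. Before clustering, power is Φ(2.802 √(133/144) − 1.960) = 77%. With 82 equal clusters, m = 266/82 = 3.24; at ICC 0.05, DE = 1.112 and power is about 72%. Of the 8-point drop from 80%, about 3 points come from attrition and the rest from clustering.

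**The case against.** The strongest counter-arguments are these.

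- **The loss may be small.** With all 82 codes and an ICC of 0.01 to 0.02, clustering costs 1 to 2 points. This stands, and is why a range is needed.
- **Some slack could sit inside 144.** If the uncorrected formula was used with a control proportion near 0.41, a design effect up to 1.09 would be covered, which with 82 equal clusters means an ICC up to about 0.09/2.51 = 0.036. The cited study's control rate is not in the document, so this cannot be excluded arithmetically. But section 2.4 describes no such allowance and presents 144 as the requirement for 80%.
- **The planned analysis is not a completers' comparison of proportions.** Section 5 analyses everyone randomised, with data to the last visit, and section 5.1 uses time-to-event methods. If all 190 per arm contributed fully, the same formula would give about 84% at ICC 0.05 and 79% at ICC 0.10 with 82 equal clusters. Deaths and withdrawals will not contribute fully, so this is an upper bound. It does shift the level of power, but it does not supply the missing allowance.
- **Clustering is handled elsewhere.** The mixed-effects model in 5.1 addresses the analysis, not the stated power. The reassessment in 5.5 is optional and does not mention clustering.

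A reader might also infer that nursing teams are the real clusters and that power collapses to around a half. The document gives no number of teams, so no such figure can be supported. The 40-cluster and CV 0.7 rows above are likewise illustrations.

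**Conclusion.** The point holds: section 2.4 states 80% power for a cluster-randomised comparison from an individual-randomisation calculation. If 144 is the number that gives exactly 80% without clustering, any positive ICC takes power below 80%. With the document's maximum of 82 codes at equal size, the loss is about 1 to 5 points for an assumed ICC of 0.01 to 0.05, and about 9 points at 0.10. It grows if codes are excluded or combined, or if cluster sizes vary.

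The documents do not support one replacement figure. In particular, it would be wrong to read the 72% above as the cost of ignoring clustering, because it includes a separate attrition shortfall. Nor do they support saying that clustering is ignored throughout the plan.

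**What to change.** In section 2.4:

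1. State the expected number of randomised clusters after any exclusion or merging, the mean analysed cluster size m and its CV, and an assumed ICC with a range and its basis.
2. Apply DE = 1 + [(1 + CV²)m − 1] × ICC, and replace the 80% with the resulting range of power for the fixed 380.
3. Report attrition on its own line: 133 per arm after 30% loss, about 77% before clustering, then the clustered figures.
4. In section 5.5, make the clustered figure the benchmark for any sample-size reassessment.

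Estimating the ICC from pooled data at the 100-subject look is tempting but should not be relied on. Over up to 82 codes that is about 100/82 = 1.2 patients per code, far too few for a usable estimate. Pooling the arms would also count the treatment effect as between-cluster variance.

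The cost is rewording and a less favourable stated power. No extra patients are needed and the analysis does not change.

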## 5. Statistical and Analytical Plans

We will implement an intention-to-treat (ITT) analysis, meaning all subjects randomized to either the intervention or control groups will be analyzed. Subjects who withdraw or are lost to follow-up will have their data analyzed up to their last recorded home nursing visit.

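### Section 2.4 is internally inconsistent: after the stated 20% mortality and 10% withdrawal, 190 enrolled per arm leaves about 133 to 137, below its own minimum of 144

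*Protocol article*

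**What the plan says.** Section 2.4 (Sample Size Estimation) sizes the trial on "an odds ratio (OR) of 2.0" for a wound-area improvement of 40% or more, with 80% power and a two-sided 5% error rate. From this it concludes that "we require at least 144 subjects per arm".

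It then allows for losses: "After assuming a 20% mortality and 10% withdrawal rate". In support it cites an earlier "study of 16% mortality and 6% withdrawal", and a second trial with 8% loss to follow-up. The result is stated as "we plan to enroll a total of 380 subjects (190 per arm").

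Section 2.1 (Study Design) repeats "the recruitment of 380 subjects (190 per arm"), and the Abstract repeats 380. No other section gives a different attrition allowance, and the step from 144 to 190 is not shown.

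**The concern.** An allowance for attrition is meant to ensure that the required number remains after the expected losses. The required number is therefore divided by the proportion expected to remain. Multiplying by one plus the loss rate always gives too few, and the gap widens as the loss rate rises. At a combined loss near 30% it is large enough to show.

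Here the three numbers in one paragraph (144 needed, 20% and 10% lost, 190 enrolled) cannot all hold. At stake is whether the stated 80% power describes the trial as planned. The figure of 380 is also the starting point for any sample size re-estimation under Section 5.5, so the same step could be carried forward.

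**Working it through.** **Inputs, all from Section 2.4:** 144 required per arm; 20% mortality; 10% withdrawal; 190 enrolled per arm; 80% power; two-sided 5%; OR 2.0. The control-arm response rate is not given.

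**1. Reproducing the plan's 190**

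| Route | Result per arm |
|---|---|
| 144 x 1.2 x 1.1 (multiplied on, in turn) | 190.08 |
| 144 x 1.30 (multiplied on, rates added) | 187.2, so 188 |
| 144 / (1 - 0.30) (divided out, rates added) | 205.7, so 206 |
| 144 / (0.80 x 0.90) (divided out, in sequence) | 200 |

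Multiplying on reaches 190, or comes within two patients of it. Dividing out by the stated rates does not. Two divisions by other rates also come close: 144 / (1 - 0.24) = 189.5, using the cited 16% mortality plus 8% loss to follow-up, and 144 / (0.84 x 0.90) = 190.5. Neither uses the 20% and 10% that the section says it assumed.

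**2. What 190 leaves under the stated rates**

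- Rates added: 190 x 0.70 = 133, a shortfall of 11 (11/144 = 7.6%).
- Rates in sequence: 190 x 0.80 x 0.90 = 136.8, a shortfall of about 7 (7.2/144 = 5.0%).

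The largest total loss that still leaves 144 is 1 - 144/190 = 24.2%. Both readings of the stated allowance (30% and 28%) exceed it.

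**3. Enrolment that would keep 144**

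206 per arm (412 total) or 200 per arm (400 total), which is 16 or 10 more per arm than planned.

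**4. Effect on power**

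Assume that 144 per arm gives exactly 80%. The standardised effect at n = 144 is then 1.96 + 0.84 = 2.80, and power at n per arm is Phi(2.80 x sqrt(n/144) - 1.96).

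- n = 133: 76.8%.
- n = 136.8: 78.0%.

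**5. Sensitivity to the missing control rate**

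These are normal-approximation results for two proportions at OR 2.0. The control rates are assumptions.

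| Assumed control rate | n per arm for 80% | Power at 133 | at 137 | at 144 |
|---|---|---|---|---|
| 20% | 172 | 69.3% | 70.6% | 72.8% |
| 30% | 141 | 77.7% | 78.9% | 80.9% |
| 40% | 133 (144 with continuity correction) | 80.2% | 81.4% | 83.3% |
| 55% | 143 | 77.2% | 78.5% | 80.5% |
| 70% | 186 | 65.9% | 67.2% | 69.4% |

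So 144 is attainable at more than one control rate and cannot be pinned down. The loss between 144 and 133 to 137 is stable, at about 2 to 3.5 points in every row.

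**The case against.** **The assumed rates already contain a margin.** At the cited 16% and 6%, 190 x 0.78 = 148, above 144. With the local one-year mortality of 14.3% in the Background and the assumed 10% withdrawal, 190 x 0.757 = 143.8, about 144. This stands as a reason to think the practical risk is small. It does not reconcile the text, which says it assumed 20% and 10%.

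**Lost subjects still contribute.** Section 5 says: "Subjects who withdraw or are lost to follow-up will have their data analyzed up to their last recorded home nursing visit". Section 5.1 uses time-to-event methods for dichotomous outcomes, and Table 2 has wound measurements from day 30 onward. A subject who dies or withdraws late is therefore not worth zero. That is fair, and it means 133 to 137 is a planning figure rather than a forecast of the number analysed. But Section 2.4 itself treats deaths and withdrawals as losses to be made good, and on that basis it replaces too few.

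**The sample size may be re-estimated.** Section 5.5 leaves this open but does not commit to it, so it does not repair the stated figure.

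**Stronger readings that the documents do not support.** A reader might take the multiplication error as established. The formula is not printed and other divisions reach about 190, so the fault could lie in the stated rates instead. A reader might also conclude that the trial cannot reach 80% power. That depends on 144 giving exactly 80%; at an assumed 40% control rate, 133 still gives 80.2% without continuity correction. Finally, a reader might fold in clustering to show a much larger loss. The article gives no intracluster correlation, so any such figure would rest on an assumed one, and clustering is a separate question.

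**Conclusion.** The inconsistency is real and follows from the section's own inputs under either way of combining the rates: about 133 to 137 per arm remain, against a stated minimum of 144. No other section resolves it.

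Its size is modest. The stated 80% becomes about 77 to 78%, a misstatement of 2 to 3 points. Those power figures assume that 144 gives exactly 80%, that every death or withdrawal counts as a full loss, and that there is no design effect. The shortfall against 144 needs only the second of these. That the allowance was multiplied on is the likeliest explanation, not a demonstrated one.

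**What to change.** Establish which of the stated figures is wrong, then make one of two changes in Section 2.4:

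- **If 20% and 10% are the intended assumptions:** state that 380 enrolled yields about 133 to 137 evaluable per arm. If 144 corresponds to exactly 80%, give the power as about 77 to 78% before any design effect for clustering.
- **If the rates are what is wrong:** replace them with a justified total attrition of at most 24%. Quoting the 24% ceiling beside an unchanged 20% plus 10% would leave the contradiction in place.

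In either case, print the inflation formula, so that any re-estimation under Section 5.5 starts from a figure that can be checked.

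The cost is a wording correction and, under the first option, a slightly less favourable power statement. Raising enrolment to 400 or 412 would also restore 144 but is not needed for consistency, and it may be hard. Section 2.5 puts the known pool at 500 to 600 people, of whom 20% to 30% are expected to be ineligible. That leaves roughly 350 (500 x 0.70) to 480 (600 x 0.80).
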